#### Data analysis

The sample size was calculated using the MVIC of the muscles as the outcome and an 80% power to detect a 20% improvement, with a 5% level of significance. Based on the study by Alfredo *et al.*[28], a minimum of 17 patients were determined for each group.

Primary (MVIC of the muscles (dynamometer) and stabilometry) and secondary (pain (digital algometer), range of motion (fleximeter), and quality of life (WHOQOL-BREF and WOMAC ) outcomes will be assessed.

Descriptive statistics will be used, and data will be summarized using mean, standard deviations, and percentiles. Normality of data distribution will be tested using the Kolmogorov-Smirnov test. Normal variables and comparison among three groups of the study will be assessed at baseline and at eight weeks follow-up using Analysis of Variance. Post-hoc tests will consist of the Turkey test for parametric variables, and the Dunn’s test for non-parametric variables, and the Dunn’s test for non-parametric variables. Data processing will be performed using the SPSS™ version 13.0 (Chicago, Illinois, United States) and the level of significance will be set to 5%.

The Cohen's d method will be used to determine the effect size. The interpretation of the values will be based on the classification established by Cohen: less than 0.2 (small effect); around 0.5 (moderate effect), up from 0.8 (large effect) [29].

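### The effect-size scale puts zero in the 'small effect' band and gives no clear label from 0.2 to about 0.5 or from there to 0.8

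*Protocol article*

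**What the plan says.** The last paragraph of the Data analysis section (protocol article, Methods/Design) fixes the measure: "The Cohen's d method will be used to determine the effect size". It then names the basis of the labels, "The interpretation of the values will be based on the classification established by Cohen", and prints the cut-points: "less than 0.2 (small effect); around 0.5 (moderate effect), up from 0.8 (large effect"). No category lies below small, and no numerical limits are set for the moderate range.

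Inference is set separately, earlier in the same section: "comparison among three groups of the study will be assessed at baseline and at eight weeks follow-up using Analysis of Variance", followed by post-hoc tests, and "the level of significance will be set to 5"%. The planned size, from the same section, is "a minimum of 17 patients were determined for each group".

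**The concern.** An interpretation scale should give every possible value exactly one label, and should not call the absence of a difference an effect. The printed scale fails on both counts.

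- **Zero is labelled an effect.** Being below 0.2 is the only condition for the small label, so d = 0.00 and d = 0.05 both meet it. If d carries a sign, every negative value meets it too, however large.
- **Two stretches have no clear label.** A value of 0.3 is neither below 0.2 nor plainly near 0.5. A value of 0.65 is neither plainly near 0.5 nor as high as 0.8.

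Two things are at stake. A reader may take a difference indistinguishable from zero for a modest treatment effect. And where no label is fixed, the analyst has to choose one after seeing the data. The scale is not tied to one endpoint, so this could recur across the two primary outcomes, the secondary outcomes and the pairwise comparisons of three groups.

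**Working it through.** **Inputs, all from the Data analysis section.** 17 per group, three groups; significance level 5%; label cut-points 0.2, about 0.5 and 0.8.

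**The plan's own figure.** The 17 per group rests on "an 80% power to detect a 20% improvement, with a 5% level of significance". The article prints no standard deviation (SD) for muscle strength, so 17 cannot be reproduced. If the 20% improvement is treated as a difference of 20 units, an assumed SD of 15, 20, 20.8, 25 or 30 gives 9, 16, 17, 25 or 36 per group. Worked backwards with the two-sided normal formula, 17 per group detects d = (1.960 + 0.842) × √(2/17) = 0.96 with 80% power. None of this bears on the labels, so 17 is taken as given.

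**Step 1: the scale as printed.**

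| Value of d | Label under the printed text |
|---|---|
| −0.9 (if signed) | small |
| 0.00 | small |
| 0.10 | small |
| 0.30 | none clear |
| 0.50 | moderate |
| 0.65 | none clear |
| 0.80 | large |

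**Step 2: how often each stretch is reached when there is no true difference.** For two groups of 17 with their pooled SD, d = t × √(2/17) = t × 0.343, where t has 17 + 17 − 2 = 32 degrees of freedom. The cut-points on the t scale are 0.2/0.343 = 0.583, 0.5/0.343 = 1.458 and 0.8/0.343 = 2.332.

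| Range of \|d\| | Probability, true d = 0 | Label |
|---|---|---|
| below 0.2 | 0.436 | small |
| 0.2 to 0.5 | 0.409 | unclear |
| 0.5 to 0.8 | 0.129 | unclear beyond about 0.5 |
| 0.8 or more | 0.026 | large |

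The four probabilities sum to 1.000. The first splits evenly by direction: 0.436/2 = 0.218, or about 22%, on each side of zero. If the rule is applied to signed d, the share below 0.2 is 0.718. If d uses the SD pooled over all three groups (51 − 3 = 48 degrees of freedom), the first two figures become 0.437 and 0.411.

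**Step 3: the same ranges when a real effect exists.** With a true d of 0.5, the probabilities in the same order are 0.17, 0.32, 0.30 and 0.21 (noncentral t). The stretches without firm limits then hold 0.324 + 0.301 = 0.625 of results, so the gaps do not matter only under the null.

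**Step 4: what the planned test would say.** An unadjusted two-sided 5% t-test needs |d| of at least 2.037 × 0.343 = 0.70. At |d| = 0.2 the p-value is 0.56, so every |d| below 0.2 has p above 0.56. Adjustment for several pairwise comparisons would raise the threshold further.

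**The case against.** The strongest case on the other side has four parts.

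1. **The label decides nothing.** Inference rests on the analysis of variance and post-hoc tests at 5%. This stands. A reader might infer that a null trial would be reported as showing that phototherapy works. The document does not support that: nowhere does it make the d label a criterion for efficacy, and step 4 shows that any result below 0.2 would be reported as non-significant.

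2. **The 44% is not a rate of false benefit.** This also stands. The figure is for |d|, so half of those results favour the comparator, and the word small carries no direction in the text.

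3. **The sentence is shorthand for a cited scale, and 'around' is deliberately loose.** This stands in part. A loose reading of about 0.5 could absorb some of each gap. It cannot repair the small band, which has a firm upper limit and no lower one. Whether the wording departs from the cited classification cannot be checked from the document, and the point does not depend on it.

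4. **A condensed article need not give every detail of d.** This stands for what is merely unsaid: which groups form the contrast, which SD is the denominator, and whether a confidence interval accompanies d. These may be in the full protocol or analysis plan and are not raised here. It does not excuse the cut-points, which the article prints and which are faulty as printed.

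**Conclusion.** The defect is real but confined to description. As printed, the scale calls any d below 0.2 a small effect, zero included, and has no clear label in two stretches. At 17 per group with no true difference, about 44% of pairwise |d| estimates would carry a misleading small-effect label beside a non-significant test, and about 41% would fall between 0.2 and 0.5, where the label is unclear. Together that is 0.436 + 0.409 = 0.845, or about 85%.

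These figures assume normally distributed outcomes with equal variance, exactly 17 analysed per group, and a pairwise d on the SD of the compared outcome. The defect in the wording depends on none of these assumptions. The hypothesis tests, the significance level and the sample size are unaffected, and the documents do not support reading this as a false efficacy conclusion.

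**What to change.** Replace the interpretation sentence with contiguous bands on |d|:

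- below 0.2: negligible, not called an effect
- 0.2 to below 0.5: small
- 0.5 to below 0.8: moderate
- 0.8 or more: large

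State that the label is descriptive only and that no efficacy claim rests on it. Because the bands are on |d|, the direction of each difference should be given next to its label.

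The cost is one sentence, with no change to conduct, sample size or any test. It should be done before results are labelled, so that no category is chosen after the data are seen.

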## Discussion

The purpose of this randomized clinical trial is to analyze the effect of the incorporation of phototherapy into a therapeutic exercise program for OA of the knee. The study will support the practice based on evidence to the use of phototherapy in individuals with a diagnosis of osteoarthritis of the knee. Data will be published after the study is completed.

## Trial status

Patient recruitment is currently underway. Started on May 2014 and expected to finish on January 2015.

## Abbreviations

FRT: Functional reach test; LEFS: Lower extremity functional scale; LLLT: Low-level laser therapy; MVIC: Maximum voluntary isometric contraction; NSAIDs: Non-steroidal anti-inflammatory drugs; NRS: Numeric rating scale; OA: Osteoarthritis; ROM: Range of motion; TUGT: Timed up-and-go test; WOMAC: McMaster universities osteoarthritis.
